## Abstract

**Background:**

Impetigo is a common and contagious bacterial skin infection, affecting children worldwide, but it is particularly prevalent in socioeconomically disadvantaged communities. In New Zealand, widespread prescribing of the topical antibiotic fusidic acid had led to an increase in antimicrobial resistance of *Staphylococcus aureus*. Alternative treatments are urgently being sought, and as impetigo is a superficial infection, it has been suggested that topical antiseptics such as hydrogen peroxide or simple wound care alone may treat impetigo while avoiding the risk of increased antimicrobial resistance.

**Methods:**

This protocol for a non-inferiority, single-blind randomised controlled trial compares topical fusidic acid with topical hydrogen peroxide and with simple wound care in the treatment of childhood impetigo. Participants are randomised to one of the three treatments for 5 days. The primary outcome is clinical improvement assessed through paired photographs analysed by graders blinded to treatment arm. The trial is based in school health clinics in an urban centre in New Zealand. Comparison of antimicrobial resistance patterns pre- and post-treatment is also performed.

**Discussion:**

Special note is made of the need to involve the communities most affected by impetigo in the design and implementation of the clinical trial to recruit the children most in need of safe and effective treatments.

**Trial registration:**

Australian New Zealand Clinical Trials Registry (ANZCTR) 12616000356460. Registered on March 10, 2016

Protocol amendment number: 05

EB and AL contributed equally as senior authors.

**Supplementary Information:**

The online version contains supplementary material available at 10.1186/s13063-022-06042-0.

## Introduction

Impetigo is a contagious superficial bacterial skin infection, predominantly affecting children [1, 2]. It is described as one of the top 50 most common diseases [3], with a global prevalence estimated at 162 million [4]. New Zealand (NZ) is a high-income country in the South Pacific with a diverse population including tangata whenua- NZ indigenous population (Māori) who make up 17% of the population. During western colonisation, NZ established the Treaty of Waitangi [5] between the Crown and Māori which ensures a legal requirement to good governance and the right to equitable health outcomes for indigenous people [6]. While the Pacific peoples of NZ (those from the Polynesian and Melanesian Pacific islands surrounding NZ) are not part of the treaty agreement, they make up a significant proportion of NZ’s population (~ 7%), and there is recognition of significant inequities for both Māori and Pacific populations and the obligation to address these. Primary care is generally funded for children under 13 years of age, but socioeconomic barriers to care are still recognised. NZ experiences a particularly high burden of skin and soft tissue infections with as many as 11% of NZ children aged under 15 years consulting their primary care provider for skin infections annually. There is an inequity in the burden of disease with the highest rates seen in children of Māori and Pacific peoples.

As a superficial infection, impetigo is frequently treated topically rather than systemically. Since the early 2000s, New Zealand has experienced high prescribing rates of the topical antibiotic fusidic acid; rates of dispensing are highest for preschool children, followed by those age 75+ and 5–14 years. Dispensing is also highest in Pacific Island and Māori ethnicities [7, 8]. Following the increase in prescribing, a subsequent rise in fusidic acid resistant *S. aureus* isolates has been reported; resistance is now demonstrated in 28% of NZ *S. aureus* isolates [9]. In 2005, a fusidic acid resistant and methicillin resistant *S. aureus* (MRSA) clone was identified and has become the dominant MRSA clone in New Zealand [10]. This suggests that widespread community use of fusidic acid has not only led to selection of fusidic acid resistant clones but also concurrent MRSA. In an attempt to limit the development of further antimicrobial resistance by avoidance of topical antibiotics, NZ has updated national impetigo guidance. While oral antibiotics remain the first line for severe or multi-lesional impetigo, topical fusidic acid is no longer first line in mild-to-moderate disease, superseded by the advice to use an antiseptic cream, 1% hydrogen peroxide [11]. The UK National Institute of Clinical Excellence (NICE) have also released a draft guideline on impetigo proposing the same change [12]. These prescribing guidelines are based on evidence from a single randomised controlled trial performed in 1993 with no information provided on fusidic acid resistance rates within the study population. This demonstrated “a tendency towards somewhat lower efficacy in [hydrogen peroxide] compared to [fusidic acid]” with no significant difference between the groups [13]. Since that time, antimicrobial resistance patterns to fusidic acid have changed within NZ [7, 8]. and potentially within other countries where it is used topically or systemically.

In the past, clinical trials of impetigo have presented challenges and this trial protocol seeks to address these. Impetigo is predominantly a disease seen in the community with primary care presentations representing only a small proportion of cases. Many families never seek medical review, particularly in populations where financial concerns limit health-seeking behaviours [14]. A clinical impetigo trial should, therefore, ideally be based within a community setting. Impetigo is a disease of childhood, a challenging group to enrol in clinical trials with previous trials on impetigo treatment including large numbers of adults; the RCT upon which the current practice is based recruited patients with a mean age of 17 years [13].

Defining primary outcomes in impetigo treatment is also challenging as demonstrated by the variety of outcomes measures across prior clinical trials. A systematic review concluded that more robust outcome measures were required [15]. Time to reported clinical endpoints have ranged between 1 and 3 weeks after starting treatment. Some trials have used complete cure while others are satisfied with clinical improvement of varying definitions. Many are based on observer defined definitions, but even the more objective scores such as the Skin Infection Rating Score (SIRS) have been used as a primary outcome measure in a variety of ways, including an absolute reduction in score, predefined absolute decrease in score, or as a percentage decrease from the baseline [6, 16].

To best inform our practice, our trial requires a majority recruitment of children of Māori and Pacific children, the groups most affected by impetigo in NZ. There are marked inequities in health outcomes for Māori and Pacific Island children, and it is critical that health research is focused on understanding and addressing these inequities. Impetigo is contributing to inequity in health outcomes and therefore is crucially important to Māori and Pacific health. With the burden of skin disease affecting predominately Māori and Pacific children, appropriate cultural engagement with these communities was recognised as a key factor, both for successful trial completion and ensuring meaningful results which will be acceptable, generalisable, and implementable for those most affected by impetigo.

### Objectives

We hypothesize both simple wound care and topical hydrogen peroxide are non-inferior to topical fusidic acid in the treatment of impetigo.

Therefore, the aims of this clinical trial are:
To compare the effectiveness of topical fusidic acid with topical hydrogen peroxide and simple wound care in the treatment of mild-to-moderate impetigo in a community with both high rates of impetigo and increasing fusidic acid resistance.

2) To examine potential changes in the antimicrobial resistance of skin pathogens in response to these different treatments for impetigo.

### Trial design

TIARA is an open label, single-blind, non-inferiority randomised controlled trial with three parallel treatment groups. The primary endpoint is clinical improvement at seven days. Randomisation is performed 1:1:1 within each school clinic.

## Methods: participants, interventions, and outcomes

### Study setting

Auckland city has a temperate climate and is a large urban centre of 1.6 million people. Primary school health clinics serve the more socioeconomically disadvantaged areas within two of the three district health boards in the Auckland region: Auckland and Counties Manukau. These health clinics provide primary care, including free skin and throat infection management, to students aged 5–13 years [17, 18]. The school nurses running the clinics are invited to participate in this study to provide a potential eligible population of ~ 10,000 enrolled students. Due to their over representation of socio-economic disadvantage, over 90% of children in the schools are of Māori or Pacific Island ethnicity, and there is a high rate of impetigo.

### Eligibility criteria

Children meeting the eligibility criteria are identified and their caregivers contacted to explain the study and obtain consent. Caregivers must provide verbal informed consent before any study procedures occur. This is then followed by written informed consent (see Appendix 1 for sample of informed consent form).

#### Inclusion criteria

Children eligible for the trial must comply with all of the following prior to randomisation:
Enrolled in one of the participating school clinicsMild-to-moderate impetigoAged 5–13 years

#### Exclusion criteria

Severe impetigo requiring oral antibiotics; defined as extensive lesions (> 3 lesions or > 5% body surface area), presence of cellulitis, or fever > 38.5 °CChildren who are immunocompromisedKnown allergy to study drugsCurrent use, or use within the previous 5 days, of topical or oral antimicrobialsCommencement of antimicrobials for other reasons during the trial periodFailure to obtain informed consent for randomisation or withdrawal of consent

Excluded children continue with treatment according to the existing school health clinic standard operating procedures (SOP).

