### Allocation concealment mechanisms and implementation

Randomisation is implemented by block randomisation within each participating school, sequence allocation code was written in R [22]. Children are randomly allocated (1:1:1) to topical fusidic acid, topical hydrogen peroxide, or simple hygiene measures. Participating schools are randomised separately to limit bias caused by excess recruitment to any individual arm within a single school*.* Allocation is performed by school nurses using the pre-generated codes contained in sealed, opaque, sequentially numbered envelopes. Both the participant and school nurse are aware of treatment allocation due to the appearance of the study medications (e.g. hydrogen peroxide has a silvery sheen) or lack of study medication in the simple hygiene measure arm. However, investigators, photograph reviewers, and laboratory staff are blinded to allocation.

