### Statistical analyses

For baseline data, d**i**chotomous variables will be summarised as proportions of patients in each treatment group, differences between groups will be assessed using a chi-square statistic, and where small cell sizes (less than 5) are present, a Fisher’s exact test will be used. Continuous variables with an underlying normal distribution will be summarised as mean and standard deviation, and differences between groups will be assessed using Student’s *t*-test. Other distributions will be either transformed if suitable and *t*-tests performed with reporting of geometric means or distributions will be reported as median and interquartile range and differences in groups assessed using Wilcoxon rank non-parametric tests with Hodges-Lehmann estimates and 95% confidence intervals.

Analysis will be performed after completion of recruitment. Both hydrogen peroxide and simple hygiene groups will be compared independently with fusidic acid with 95% confidence interval. Non-inferiority will be defined as a treatment success rate of no more than 10% below that of the fusidic acid success rate. An intention to treat and per protocol analysis will be performed using all patients with available primary outcome data. Patients without primary outcome data or for whom caregivers withdrew consent to participate will not be included in the analysis.

To investigate predictors of treatment success, backwards stepwise random-effects logistic regression will be performed on a priori and other variables identified as different in baseline characteristics between randomisation groups.

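### Starting an antimicrobial after randomisation is written as an exclusion criterion, and the analysis sections do not agree on whether such a child is analysed

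*Protocol article*

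**What the plan says.** The Inclusion criteria section says that eligible children "must comply with all of the following prior to randomisation". The Exclusion criteria section then lists commencement "of antimicrobials for other reasons during the trial" period. Current use, and use in the previous 5 days, form a separate item, so this one refers to treatment begun after enrolment. The same section adds: "Excluded children continue with treatment according to the existing school health clinic standard operating procedures (SOP").

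On who knows the arm, Allocation concealment mechanisms and implementation states: "Both the participant and school nurse are aware of treatment allocation". Blinding covers others: "investigators, photograph reviewers, and laboratory staff are blinded to allocation". Study setting says of the school clinics: "These health clinics provide primary care, including free skin and throat infection management".

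On analysis, Statistical analyses states: "An intention to treat and per protocol analysis will be performed using all patients with available primary outcome data". It omits only children without primary outcome data and those whose caregivers withdrew consent. Sample size defines later exclusions and losses as no day-7 follow-up or the lack of two images. Neither section mentions a new antimicrobial. Primary outcome methods counts a child taken off the trial protocol early for clinical deterioration, by a school nurse or general practitioner, as a treatment failure.

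**The concern.** An exclusion criterion should be a fact that can be established before allocation. This one is an event that follows allocation and may depend on it. Two problems result.

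First, the primary analysis set is ambiguous. For a child who starts an antimicrobial and is still photographed on day 7, the eligibility section says excluded and the analysis section says included. The choice could be made after the data are seen.

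Second, the label on the event matters. An antimicrobial started because the impetigo worsened leads to a failure. One started for another reason leads to an exclusion. In an open-label setting, a child on wound care alone may be given an antimicrobial more readily, or the indication may be recorded differently. If the children who drop out this way would have done worse than their arm average, the remaining children look better. In a non-inferiority trial that error favours the claim. The same route is open in the hydrogen peroxide arm.

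**Working it through.** **Step 1: the sections side by side, for a child who starts an antimicrobial for another reason on, say, day 3 and has both photographs.**

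- Exclusion criteria: excluded, and treated under the clinic's usual procedures.
- Inclusion criteria: was eligible, because eligibility was judged before randomisation.
- Sample size: not a later exclusion, because follow-up and both images exist.
- Statistical analyses: in the analysis, because primary outcome data exist and consent stands.

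The status of this child cannot be settled from the text.

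**Step 2: the plan's own figures.** Sample size gives 160 evaluable per group, 80% success on fusidic acid, a 10% margin, one-sided alpha 0.05, and 178 recruited to allow for 10% loss. The loss step reproduces: 160/0.90 = 177.8, rounded up to 178. The 160 does not follow from the other inputs: (1.645 + 0.842)² × (0.16 + 0.16)/0.10² = 198 after rounding up. That is a separate matter. Here 160 is used because it is the planned size.

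**Step 3: possible size of the bias.** The protocol gives no rate of antimicrobial starts, so the following are assumptions:

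- true success is 80% on fusidic acid and 70% on wound care, which is exactly at the margin;
- a fraction e is excluded from the wound-care arm only;
- success among the excluded children is f.

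Observed wound-care success is p = (0.70 − e·f)/(1 − e). The standard error is SE = √(0.80×0.20/160 + p(1 − p)/160). The chance of a false claim is Φ[(p − 0.80 + 0.10)/SE − z], with z = 1.645 (one-sided 0.05) or 1.960 (two-sided 95% interval).

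For e = 5% (eight of 160 children) and f = 40%:

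- p = (0.70 − 0.05×0.40)/0.95 = 0.716, a difference of −8.4 points;
- SE = 0.0477, and 0.0158/0.0477 = 0.331;
- Φ(0.331 − 1.645) ≈ 0.095 and Φ(0.331 − 1.960) ≈ 0.052.

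| Excluded (f = 40%) | Observed success | False claim, one-sided 0.05 | False claim, two-sided 95% interval |
|---|---|---|---|
| 0% | 70.0% | 5.0% | 2.5% |
| 2% | 70.6% | 6.5% | 3.3% |
| 5% | 71.6% | 9.5% | 5.2% |
| 10% | 73.3% | 17.4% | 10.5% |

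Reducing the wound-care denominator for the excluded children changes little: at one-sided 0.05 it gives 9.4% for 5% excluded and 16.9% for 10%. The 10% row uses the whole of the protocol's allowance for losses on this one cause, so it is an extreme case.

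**Step 4: dependence on f.** With 5% excluded and one-sided 0.05, the false-claim rate is about 19% if every excluded child would have failed (f = 0), about 10% at f = 35%, and 5% at f = 70%. At f = 70% exclusion is unrelated to outcome, p stays at 0.70 and nothing is inflated.

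**The case against.** The strongest reply is that the protocol never says these children leave the analysis. Statistical analyses, read alone, keeps any child with primary outcome data, and Sample size does not list the event either. That is correct. A reader might infer from the exclusion list that the intention-to-treat set drops them, but the documents do not establish this. They establish a conflict between sections.

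Next, the obvious bias route is partly closed. Children removed because the impetigo got worse are counted as failures, and the criterion is limited to other indications. This also stands. Bias needs starts, or their attribution to another reason, to differ by arm and to be related to outcome. The protocol does not show that this happens. It also contains no safeguard against it, although the Discussion admits possible bias from early removal by unblinded staff.

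A reader might also infer that unblinded staff control the event. The nurse and participant know the arm, and the clinics manage skin and throat infections. But the protocol does not say who starts antimicrobials for other reasons. A general practitioner could, and whether that prescriber knows the allocation is not stated. What can be said is that nobody described as blinded is given this decision.

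Finally, the item on withdrawal of consent in the same list is also a post-randomisation event. Statistical analyses deals with it explicitly, so moving it would tidy the list but change no result.

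**Conclusion.** The point holds as a defect of definition with a possible bias, and it should be corrected. A post-randomisation event, in a trial where nurse and participant know the arm, is written as an eligibility exclusion. The Exclusion criteria, Sample size and Statistical analyses sections give different answers for the same child.

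The direction of harm is towards non-inferiority only if exclusions fall more on the non-antibiotic arms and among children who would have done worse. The size cannot be read from the protocol. The illustration of 5% excluded (5% to about 9.5%, or 2.5% to about 5.2%) rests on one-arm exclusion and on 40% success among the excluded, neither of which the documents support or rule out. The two pairs are shown because Sample size uses one-sided 0.05 while Statistical analyses plans a 95% interval. To conclude that the randomised comparison is destroyed would go beyond the evidence.

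**What to change.** 1. Limit the exclusion criteria to facts known before randomisation.
2. Define the start of a new antimicrobial as a post-randomisation event. Still take the day-7 photographs, analyse the child in the allocated arm in the intention-to-treat set, and leave the child out of the per-protocol set only.
3. Report these starts by arm and by recorded reason, so that a difference between arms can be seen.
4. Reconcile the Exclusion criteria, Sample size and Statistical analyses sections so that each child has one status.

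This concerns follow-up and analysis sets only and does not touch clinical care. The cost is wording: the day-7 visit and photographs are already scheduled, and both analyses are already planned. There is a small downside. Antimicrobials taken alongside the trial treatment can dilute the intention-to-treat contrast, which in a non-inferiority trial also leans towards the claim. The planned per-protocol analysis addresses this. Because that set carries the selection described above, the two analyses should be read together with the counts by arm.

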### Intervention

All lesions are cleaned with saline and scabs gently removed. For the group randomised to fusidic acid, 2% fusidic acid ointment (DP Fusidic Acid, Douglas Pharmaceuticals Ltd, Auckland, NZ) is applied topically, and for the hydrogen peroxide arm, 1% hydrogen peroxide cream (Crystaderm, AFT Pharmaceuticals, Auckland, NZ) is applied topically. In both cases, an adequate amount to cover each lesion is used and dressing(s) then applied. A tube of appropriate topical medication is supplied for the child and/or caregivers to continue applications twice daily for 5 days with dressing changes. Participants allocated to simple hygiene measures receive no medication but a dressing is applied following the cleaning of the lesion(s). All participants are provided with supplies to allow them to clean and redress the wound twice daily for 5 days. Low adherent wound pads are used so as not to interfere with the wound healing process. In all groups, scabies is treated if present.

### Modifications

All adverse effects, including pain, itch, or allergy to study medication, will be reported; the study medication must be withdrawn and the patient changed to routine treatment as per the SOP of the health clinic. If clinical deterioration while on study medication is identified by the school nurse, the study medication may be withdrawn at the nurse’s discretion. In this case, the patient will be changed to routine treatment as per the standard operating procedures of the health clinic.

### Adherence

Face-to-face reminders of adherence are provided by nurses at both day 0 and day 2 visits, and adherence over the trial period is assessed on days 2 and 7. Sticker charts are provided for each participant to encourage adherence.

### Participant timeline

On the first visit (day 0), demographic data, inclusion and exclusion criteria, and verbal consent are obtained. All lesions are cleaned and the single largest lesion is photographed using a digital camera, and a bacteriological swab is taken from the same lesion as the photograph. The patient is then randomised and the appropriate treatment is commenced and continued for 5 days. Two days after enrolment into the trial (day 2), a safety check is performed by the school nurse to assess for rapid worsening of the impetigo or for adverse effects. The safety check can be performed between days 2 and 4 if necessary to allow for day 2 falling on a weekend. Caregivers are asked to contact the school nurse between visits, if they have concerns about the lesion getting worse. Seven days after commencing the trial (day 7), the participant is re-assessed by the nurse. A second set of photographs and repeat bacterial swab is taken from the same lesion as originally documented. Both child and caregiver complete a verbal questionnaire. Caregivers can withdraw a participant from the study at any stage. For the full schedule of interventions and assessments see Figs. 1 and 2.

